# Study protocol for a pragmatic parallel-group randomised controlled trial to evaluate the effectiveness of coaching with an online intervention, compared with the online intervention alone, for families of children who have experienced developmental regression

**DOI:** 10.1136/bmjopen-2025-105615

**Published:** 2026-06-10

**Keywords:** Parents, Psychosocial Intervention, Developmental neurology & neurodisability, Rare Diseases, Telemedicine, eHealth

## Abstract

**Introduction:**

Developmental regression is when children lose one or more skills they have established. Families caring for these children need timely recognition to assist diagnosis and tailored interventions. Families also need support to develop practical skills for caregiving and strategies to promote family well-being and community participation. Given the high caring demands, flexibly delivered approaches are needed to accommodate family routines. Online delivery of health-related interventions that provide coaching, information, or both has been found to be a feasible and effective option for families. Family Focus is a new family-centred online programme, co-designed with parents and family advocates, clinicians, and researchers to support and empower primary carers.

**Methods and analysis:**

This study is a prospective, pragmatic randomised controlled trial comparing the effectiveness of online parent coaching plus Family Focus (Coaching+FF) to Family Focus alone (FF) for primary carers of children experiencing developmental regression. A sample of 56 families will be randomised in a 1:1 ratio. Outcomes are assessed at baseline, post-intervention and 12-month post-randomisation. The primary outcome is parental stress symptoms at post-intervention. Secondary outcomes include parental depressive and anxiety symptoms, parental engagement in health-promoting activities, family empowerment, family quality of life and child global health outcomes. The study will also examine the uptake and acceptability of specific coaching and FF components and explore the facilitators and barriers to their delivery and implementation.

**Ethics and dissemination:**

Ethics approvals were obtained from the participating organisations (Monash Health HREC/107806). Informed consent is obtained from parents/guardians of children prior to study enrolment. Study findings will be disseminated through peer-reviewed publications, conference presentations and lived experience agencies.

**Trial registration number:**

ISRCTN25513446.

STRENGTHS AND LIMITATIONS OF THIS STUDYThis will be the first study using a randomised controlled trial and mixed-methods design to assess the effectiveness of an online programme for reducing parental stress, with and without coaching, in parents of children with developmental regression.A key strength of the study is the codesign of the programme with an advocacy and research-driven non-profit organisation and families of children experiencing developmental regression, in partnership with clinician researchers.The time interval between onset of developmental regression and the start of the intervention will vary among participants. As participants enrol one at a time in this trial, it is impractical to use stratified randomisation based on different time intervals.While the implementation of strategies to recruit, engage and retain participants has been included, lower than expected recruitment would limit the scope of the analyses and conclusions.

## Introduction

 Developmental regression (hereon, ‘regression’) is broadly described as the loss of previously established abilities or skills in children. Early signs of regression may not be apparent to parents and thus may result in delayed presentations to child health services.^1^ In particular, very young children, particularly those with delayed skill acquisition, have fewer abilities to lose, and so their regression may be less obvious.^2^ Families may also encounter delayed assessment, as there is often no specific pathway established for addressing presentations of regression unless the regression is sudden and severe, indicating a potential neurological emergency. This can lead to delayed care, increased stress for families and missed opportunities for early intervention.

Children presenting with regression may have a neurodevelopmental condition^3^ or a childhood dementia condition—an umbrella term that refers to a group of progressive neurodegenerative diseases.^4^ Both types of conditions will benefit from early identification and prompt intervention. Timely investigation may identify a diagnosis and empower a family with knowledge to make informed decisions about interventions and future reproductive choices, as well as offer insights for extended family members. Compared with observing delayed development from the outset, witnessing a child lose skills they had attained as the onset of a condition has been linked with increased levels of parental distress, particularly given the uncertainty around their child’s diagnosis and prognosis following skill loss.^5^ When a treatable cause is not found, the distress and shock families experience can be heightened.^6^ Families caring for children experiencing regression require timely recognition and support, along with the skills to promote their child’s care and development. They also need support to navigate services, maintain family health and well-being, and foster community inclusion and participation.^7^ Health education, psychoeducation and health promotion programmes are essential in supporting parent mental health^5 8^ and play a fundamental role in early intervention and the overall support provided to families of children experiencing regression.^6^

Family-centred approaches that build the capacity of parents to care for their child are considered best practice when working with children and families.^9 10^ One capacity-building approach commonly used within the context of paediatric practice is coaching with parents. Research has shown coaching can be an effective method for supporting progress towards parent goals and improving parental sense of competence, confidence and engagement.^11 12^ A recent review of coaching provided by allied health professionals in paediatrics highlighted inconsistency in definitions of coaching.^8 13^ Akhbari Zeigler and Hadders-Algra^13^ recommend that parent coaching should refer to support for families that is relationship-based, family-centred and where the overarching goal is the optimal participation of the child and family in daily life and empowerment of the family to support the child’s development. During coaching it is recommended that a collaborative relationship be developed, in which parents are supported to make informed decisions through guidance from the coach.^13 14^ In this context, coaching incorporates joint planning, observation, action, reflection and reciprocal feedback.

However, families with intensive caregiving tasks can experience barriers to accessing in-person supports such as coaching, health or psychoeducation programmes or specific skill training to support their child’s development.^15 16^ Technology-assisted parenting programmes have been recently recognised by the United Nations as a way of delivering support for families, made possible by increased parental digital literacy and accessibility.^17^ Consumer surveys of Australians in 2021 and 2022 revealed a significant increase in consumers who are not only open to but are actively seeking healthcare through videoconferencing, remote monitoring and asynchronous communication with clinicians.^18^ This rise in consumer demand for virtual care indicates a growing acceptance and comfort with virtual healthcare.^18^ Flexible access to technology-based services is an opportunity to increase timely access to intervention^19^ to improve health outcomes for children experiencing regression and their families.

Evidence is rapidly emerging that online interventions are effective in improving parenting, supporting parent health, and promoting parent mental health and wellbeing.^20^,^22^ Research also shows that interventions led by parents can improve the physical and mental health of children.^23^ A recent systematic review and meta-analysis of interventions for parents reported that online interventions that are combined with health professional contact or consultations (blended care) were adopted in 22 of the 30 studies in the review.^20^

Blended care is fast becoming common practice in the current technological age, combining online components for assessment, psychoeducation, skills training and therapist guidance provided either in person or virtually.^24^ This approach enhances the support provided for applying skills. A systematic review reported that guided digital mental health interventions for youth and young adults, using a combination of asynchronous (online content) with synchronous (in-person online) support, had higher rates of completion.^25^ While past studies did not explicitly report effect sizes within guided groups (eg, completers vs non-completers), the literature suggests that completers in guided interventions likely achieve better outcomes due to higher adherence to the intervention content and procedure.^26^ A recent three-arm randomised controlled trial of a web-assisted intervention for parents of children with attention-deficit/hyperactivity disorder and oppositional defiant disorder found that the arm that received a guided intervention was more effective in reducing blinded clinician-rated externalising symptoms than the unguided or usual care control groups.^27^ However, the study noted that other similar studies of guided online interventions had contradictory findings and that further research is needed to compare guided and non-guided online interventions.

To empower and support primary carers of children experiencing regression, we designed an online, self-paced programme—Family Focus (FF). The programme’s content and delivery were informed by insights gained from a review of the literature of parent-focused or family-focused online, self-paced support to identify the most important information for parents caring for children with complex developmental needs.^20 28^ This novel, codesigned online multimedia programme is designed to build on parents’ strengths, foster resilience, enhance coping strategies and well-being and promote meaningful participation for both the child and family in daily life and the community. When combined with one-on-one parent coaching support (Coaching+FF), families might engage with a personalised family-centred experience. To support this, we drew on existing literature and models on coaching^29 30^ and developed a protocol for offering individualised, online coaching to parents.

### Aim and objectives

This study aims to evaluate the effectiveness and uptake of a blended approach (Coaching+FF) for primary carers (hereon, ‘parents’) of children experiencing developmental regression, compared with the online programme alone (FF). By using an active comparator in this study, we aim to generate clinically relevant and realistic estimates of the effects of blending coaching and the online intervention,^31^ over and above the effects of the online intervention alone. This approach acknowledges the urgent need for support among families managing child regression concerns and provides a practical framework for evaluating new intervention strategies in this context.

In comparison to parents who engage with FF without coaching (‘comparison group’), the objectives are to determine:

The effects of Coaching+FF (‘intervention group’) on the primary outcome of parental stress symptoms.The effects of Coaching+FF (‘intervention group’) on the secondary outcomes of (1) parental anxiety and depressive symptoms, (2) family empowerment, (3) parental engagement in health-promoting activities, (4) family quality of life and (5) child’s global health outcomes.

We will also explore the proportion of parents in the FF group who transition from above to below the clinical thresholds for stress, anxiety and depressive symptoms at post-intervention. In addition, the uptake and acceptability of online parent coaching and the FF programme will be examined by assessing recruitment and retention rates, user engagement metrics, coaching uptake, programme usage data and participant feedback on perceived usefulness and satisfaction at post-intervention.

We hypothesise that, compared with parents in the FF group, parents in the Coaching+FF group will report lower levels of parental stress, anxiety and depressive symptoms, and greater improvements in family empowerment, engagement in health-promoting activities, family quality of life and child’s global health outcomes. These differences are expected to emerge at post-intervention and follow-up. Further, we anticipate that parents would find online coaching and the FF programme satisfactory and acceptable.

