### Study procedures

#### Enrolment and randomisation

Eligible parents of children assessed through the research-embedded Developmental Regression clinic will be provided with information about the intervention trial and invited to participate. For those who consent to this study, if data on the outcome measures were collected as part of their first assessment or a follow-up review at the clinic within the past 6 months (whichever is closer to their study enrolment), the data will be transferred and used as their baseline data (T0) in the trial. Specifically, direct identifiers (eg, names) will be replaced by a code before participant data are transferred to a research-only database using REDCap, a secure, web application to support data capture.^40^ A 1:1 randomisation allocation sequence will be computer-generated within REDCap to allocate parent participants to the FF group or Coaching+FF group, thereby ensuring that participants, coaches, trial coordinator, outcome assessors and the research team analysing the data are concealed from the group assignment until baseline assessment and allocation are completed. Outcome assessors (clinicians completing assessments of the child) will remain blinded to group allocation across the assessment timepoints.

Participants will also complete post-intervention (T1) and follow-up (T2) assessments via online questionnaires hosted in REDCap. Figure 2 outlines the participant flow.

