### Data analysis

Missing data, participant dropout and loss to follow-up will be minimised through careful trial management. Additionally, the rates of missing data on individual data collection forms will be monitored at each time point throughout the study.

The primary analyses will be undertaken on an intention-to-treat basis. Participant characteristics, participant engagement and intervention usage, and coaching acceptability will be described. A 2 (Group)× 3(Time) repeated measure ANOVA will be applied to compare continuous scores for primary and secondary outcomes between the intervention and comparison groups.

To explore possible attrition biases, we will also conduct analyses to compare retained participants and those lost after baseline assessment, using *t*-tests for continuous measures and chi-square-tests for categorical variables (eg, gender, family socioeconomic and clinical factors). Qualitative data collected using semi-structured interviews (eg, transcripts) will be examined by thematic analysis.

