### Risk monitoring

Given the security and privacy procedures outlined in this protocol, there is low–moderate risk to children/families of any harm, inconvenience, or discomfort resulting from participation in the trial. Information regarding potential risks, risk mitigation measures and contact helplines are included in the Participant Information and Consent Form. Further, a trauma-informed approach was applied in designing the online portal where participants access the FF programme. Specifically, features to guide participants on taking breaks from the material and information about supportive helplines and health services were identified to assist participants who might experience feelings of grief or trauma when engaging with the material. If coaches identify any issues of concern regarding a parent, they will recommend they access a relevant community service (eg, present to the local emergency department, contact their treating general practitioner or provide information on helplines). Coaches will have access to discuss any such issues with a senior psychologist on the research team if required. If an assessment shows a score that falls outside the normal limits, participants may be offered feedback, further support and referrals to relevant services.

A data monitoring committee was not considered, as this is a low-risk research study. All standard operating procedures will be documented and provided to research team members who are directly involved in the study. All risks and adverse events, including unexpected side effects, will be monitored and documented by the clinic/trial coordinator, who will act in accordance with the risk management plan. Any significant safety issue or protocol deviation that adversely affects participant safety or the ethical acceptability of the trial will be reported to the investigators and the relevant Human Research Ethics Committee. In the event of new risks or adverse events being identified, the risk management plan will be appended with a course of action. Protocol amendments are communicated to clinical and research team members by the clinic/trial coordinator through email notifications describing the changes and any impacts to operations. These email notifications will include the updated protocol and relevant updated study documents.

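### The exploratory count of parents moving below the clinical thresholds is tied to the FF arm alone, so it is an uncontrolled one-way pre-post figure that would exceed zero without any effect

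*Protocol article*

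**What the plan says.** Aim and objectives lists the between-group objectives and then adds: "We will also explore the proportion of parents in the FF group who transition from above to below the clinical thresholds". The scales named are the three DASS-21 scales (stress, anxiety, depression), and the time point is T1.

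The article uses the term FF group for one of the two arms. The hypothesis in the same section reads "compared with parents in the FF group, parents in the Coaching+FF group will report lower levels of parental stress", and Enrolment and randomisation describes a sequence "to allocate parent participants to the FF group or Coaching+FF group". The comparator is active ("By using an active comparator in this study"), so neither arm is untreated.

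Data analysis plans a 2 (group) by 3 (time) repeated-measures ANOVA, which "will be applied to compare continuous scores for primary and secondary outcomes between the intervention and comparison groups". The primary and secondary outcomes include all three DASS-21 scales. The article states no threshold-transition figure for Coaching+FF, no between-arm comparison of transitions and no count of parents who cross upward.

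**The concern.** Take parents who score above a cut-off at T0 and count those below it at T1. The count will be positive whenever the two scores are imperfectly correlated, because some of the high T0 scores were high by chance or on a bad day. Unless the same count is made in a concurrent group, this cannot be separated from benefit. Counting only downward moves also hides the parents who cross the other way.

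Other features of the protocol add causes of downward movement that are not FF. The T0 score may be a clinic measurement taken "within the past 6 months (whichever is closer to their study enrolment"), which would tend to lower its correlation with T1. Children are reviewed at the clinic during the trial. Under Risk monitoring, "If an assessment shows a score that falls outside the normal limits, participants may be offered feedback, further support and referrals" to services, so the parents in this count are those most likely to be offered other help.

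At stake is the interpretation of one exploratory result. A within-arm recovery proportion is easily taken as support for FF alone, and this design has no arm without FF against which to judge that.

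**Working it through.** **Plan's own figure.** The protocol states no expected transition proportion, so there is nothing to reproduce. What follows shows how large the figure could be with no effect at all.

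**Inputs.**
- From the protocol: 28 parents per arm (Sample size); DASS-21 at T0 and T1 in both arms (Outcomes and other measures, Table 2).
- Assumed, because the documents do not give them: T0 and T1 scores bivariate normal with the same mean and SD at both times; T0-T1 correlation r of 0.5 to 0.7; threshold c at 0, 0.5 or 1 SD above the mean. The real scale is seven items scored 0-3, so it is discrete and bounded, and normality is an approximation.

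**Formulae.**
- Share above threshold at T0: p = P(Z > c).
- Share of all parents moving down: D = p − P(T0 > c and T1 > c).
- Share of those above at T0 who move down: D / p.

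| c (SD above mean) | p | r | P(both above) | D, all parents | D / p, those above at T0 |
|---|---|---|---|---|---|
| 0 | 0.500 | 0.5 | 0.333 | 0.167 | 0.333 |
| 0.5 | 0.309 | 0.5 | 0.163 | 0.145 | 0.471 |
| 1 | 0.159 | 0.5 | 0.063 | 0.096 | 0.606 |
| 0 | 0.500 | 0.7 | 0.373 | 0.127 | 0.253 |
| 0.5 | 0.309 | 0.7 | 0.198 | 0.111 | 0.360 |
| 1 | 0.159 | 0.7 | 0.084 | 0.075 | 0.471 |

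With no effect, therefore, 25-61% of those above threshold at T0, or about 7-17% of all FF parents, would be counted as having moved below it. The sentence in the article does not say which denominator it means.

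**Upward movement.** With the same distribution at both times, the share crossing upward equals D. Take 40% above threshold and r = 0.6: P(both above) = 0.257, so D = 0.400 − 0.257 = 0.143. About 14% of all parents move down and 14% move up, for a net change of zero. The one-way count shows only the first 14%.

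**Precision in one arm.** In that case 0.40 × 28 ≈ 11 parents start above threshold and 0.143 × 28 ≈ 4 move down. Four of 11 is 36%, with an exact 95% CI of 11% to 69%.

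**Both arms.** Under randomisation, regression to the mean is expected to be the same in each arm, so its expected contribution to the between-arm difference is zero. The comparison would be imprecise. With 4 of 28 moving down in each arm, the SE of the difference is √(2 × 0.143 × 0.857 / 28) ≈ 0.094, so the 95% CI is about ±18 percentage points before any attrition.

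**The case against.** A reader might infer that the randomised evidence on these scales will not be shown. The document does not support that. Data analysis plans an intention-to-treat, between-group comparison of the continuous stress, anxiety and depression scores. What is missing is a controlled version of one dichotomised, exploratory summary.

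A reader might also infer that the authors intend to offer the proportion as proof that FF works. The article does not say so. The analysis is introduced as exploration, after the listed objectives, and apart from acceptability every hypothesis sets Coaching+FF against FF. The risk of misreading is real but is not a stated plan.

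Naming only the FF group may be a drafting slip, since both arms use the programme. That is plausible, though nothing in the text settles it. If it is a slip, the sentence still needs the same correction.

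Confidence intervals, baseline adjustment and reporting of upward moves are details that a statistical analysis plan can supply, and their absence from an article is not a fault. The choice of one arm and one direction is different, because the article itself fixes it and a later plan that followed the wording would inherit it.

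Finally, the illustrated sizes need an unchanged mean. Stress could rise over time in families of children with progressive conditions, and the downward share would then be smaller. The objection to the size stands. The uncontrolled, one-way nature of the count does not depend on it.

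**Conclusion.** The point holds as a minor one. As written, the threshold analysis is a one-arm, one-direction pre-post proportion in the comparison group, and it would be above zero from regression to the mean alone for any T0-T1 correlation below 1 with an unchanged mean. The ranges of 25-61% (those above at T0) and 7-17% (all FF parents) are illustrations that rest on assumed correlation, threshold location and normality. They are not predictions for this trial.

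The primary comparison, the sample size and the planned randomised analysis of continuous scores are not affected.

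**What to change.** In Aim and objectives, replace the reference to parents in the FF group with parents in each randomised group. State the denominator. Report downward and upward transitions, or more simply the T1 proportion above threshold, in both arms for each of the three scales, with the between-arm difference and its 95% CI. Say that any within-FF proportion is descriptive and is not evidence that FF is effective.

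No new data are needed, because DASS-21 is already collected at T0 and T1 in both arms. The cost is a change of wording and a somewhat larger exploratory table, with estimates that will be imprecise at 28 per arm.
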